### Patient and Public Involvement

Patients and public are not involved in the design or recruitment of other participants of this study. However patients are considered in adapting the intervention.

### Setting

All mothers or pregnant women who attend one of the selected healthcare centers are invited to participate in the study. The data collection was initiated in June 2017 and will continue until November 2019.

### Training Program for Healthcare Professionals

Several meetings with the participating healthcare centers take place to plan and share the logistics and the project organization with the professionals involved.

The Observatory of Perinatal Clinical Psychology, thanks to the collaboration with the Italian National Institute of Health, forms all of the healthcare professionals who are involved in the study through two specialist training courses.

The first course is 1 day of face-to-face training focused on the promotion of perinatal mental health awareness and screening. The following topics are covered: methodologies, tools, theoretical and applicative study material, to be used during the clinical practice to identify the risks of perinatal anxiety and depression. The educational objectives are: to improve knowledge of the main theories on perinatal depression and anxiety; to improve knowledge about perinatal screening procedures, to improve maternal awareness regarding perinatal depression and anxiety and to screen and evaluate the psychosocial risk factors. A further 3-day face-to-face training course is provided to the psychotherapists only, and focused on Jeannette Milgrom’s psychological intervention for perinatal depression and anxiety (Milgrom et al., 1999, 2015a,b; Milgrom and Gemmil, 2015). Particular attention is also focused on how to conduct a clinical interview in perinatal populations. The course topics are: understanding the main elements and characteristics of the intervention program and the management of perinatal depression and anxiety; perinatal depression and anxiety assessment; clinical interviews with mothers; and application of the psychological intervention to mothers, also involving the babies and fathers.

During the study, there is regular contact between the coordinating center (the Observatory of Perinatal Clinical Psychology), the Italian National Institute of Health and the eleven participating healthcare units in Italy. Monthly Skype conference calls, Webex teleconferences, telephone consultations and periodic meetings are organized to keep all participants abreast of project progress and the stages of recruitment.

### Selection Criteria

#### Inclusion Criteria

Mothers are eligible for inclusion in the study if they meet the following criteria: (1a) they are pregnant or (1b) they have a biological newborn aged ≤6 months; (2) they are able to speak and read Italian.

#### Exclusion Criteria

Mothers are excluded if (1) they have psychotic symptoms; (2) they exhibit non-suicidal self-harming or suicidal behavior; (3) they have issues with drug or substance abuse.

### Procedures

This five-phase study comprises a perinatal mental health awareness period, a screening period (up to the baby’s first vaccination), a psychodiagnostic evaluation, an intervention period (10 weeks’ duration), and a post-intervention follow-up (up to 12 months from the end of intervention). The timeline of the whole procedure is depicted in Figure 1.

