This clinic-based group intervention is led and facilitated by a licensed psychotherapist and consists of ten weekly sessions of 90 min exclusively dedicated to the pregnant women/new mothers, three sessions involving the partners/fathers, and another three sessions dedicated to mother–child interaction. [In our study, before this last module, the QUITs (Axia and Weisner, 2002) is administered to assess infant temperament traits]. The content of the individual counseling is the same as that of group-based counseling and consists of ten sessions of 60 min. At the end of each session, participants receive information and activity materials to be used in the next session. Between sessions, participants are encouraged to put what they have learnt/experienced during the treatment into practice in everyday life. The session program is shown in Table 2.

**TABLE 2 T2:** Treatment Program.

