**Additional clinical forms with the presence of children: baby H.U.G.S**	

Session 1	**Let’s play! Games and physical contact.** *The therapist introduces neonatal massage technique and talks about the feelings generated by of physical contact. Parents are presented with games for different ages and emphasis is given to the pleasure of proper mother–child interaction and the importance of non-verbal communication*.
Session 2	**Let’s learn something about our child. Observing and understanding his/her signals.** *Activities involving non-verbal interactive behavior are recommended, including stress responses. Parents are encouraged to observe and interpret the child’s non-verbal communication in a playful and fun context. The therapist introduces stimulation activities to identify differences in temperament*.
Session 3	**Let’s analyze our feelings. Parental responses to the signals of their newborn.** *Couples are encouraged to observe the differences between their needs and those of their newborn baby*.

In Italy, following the publication of the Italian language manual (Milgrom, 2003), the actual feasibility and effectiveness of Milgrom’s psychological interventions for the prevention and treatment of postpartum depression has been demonstrated by ISS research (Mirabella et al., 2016).

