#### Phase 5: Follow-up

Changes in the patients’ clinical conditions are re-evaluated at three points of follow-up (end of intervention, 6th month and 12th month) using EPDS, PHQ-9, STAI, WHOQOL-BREF, QUITs, MINI-Plus and a clinical interview.

Mothers who are still depressed after the intervention phase are sent to a clinical psychological or psychiatric service.

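### The ten-week intervention period does not fit the whole described programme for most antenatal starts, the visible text does not say which session defines T1, and the pooled pre–post analysis mixes changes that span birth with changes that do not

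*Protocol article*

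**What the plan says.** Three parts of the protocol article bear on when treatment ends.

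- **Procedures** gives "an intervention period (10 weeks’ duration", and then a "post-intervention follow-up (up to 12 months from the end of intervention".
- **Phase 4: Intervention** says that the group programme "consists of ten weekly sessions of 90 min exclusively dedicated to the pregnant women/new mothers", plus "three sessions involving the partners/fathers, and another three sessions dedicated to mother–child interaction". It treats the mother–child sessions as the final module: "In our study, before this last module, the QUITs" are given. Individual treatment is said to have the same content, yet it "consists of ten sessions of 60 min". In Table 2 the mother–child block is headed "Additional clinical forms with the presence of children: baby H.U.G.S", and one of the partner sessions deals with the couple's relationship since the birth.
- **Phase 5: Follow-up** sets "three points of follow-up (end of intervention, 6th month and 12th month", with the infant-temperament questionnaire (QUIT) among the instruments.

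The Data Analysis Plan labels these points T1, T2 and T3. It specifies a repeated-measures ANOVA against the initial score and a Cohen's d at each follow-up. The paragraph on effectiveness makes no distinction between women treated in pregnancy and women treated after birth. The inclusion criteria admit pregnant women without a gestation limit, and mothers of infants up to 6 months old. Hypothesis 4 is specifically about antepartum women.

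**The concern.** T1 is the first effectiveness assessment, and the 6- and 12-month points are counted from the same end. If the end of the intervention is not tied to one identifiable session, centres can place T1 differently. A woman treated in pregnancy could have her T1 before delivery, with a module still to come, or after delivery once that module is done. These assessments measure different things.

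The protocol itself expects depression to differ across birth. Hypothesis 1 expects higher rates in pregnancy, while the Data Analysis Plan cites higher risk postpartum. The two disagree on direction, but neither supports treating birth as neutral for the outcome. There is no control group, so a mood change that accompanies birth enters the pre–post estimate directly. The antepartum claim in Hypothesis 4 is the most exposed.

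**Working it through.** **Inputs from the protocol article:** ten-week intervention; 10 weekly core sessions; 3 partner and 3 mother–child sessions with no stated spacing; mother–child module last and with children present; enrolment in pregnancy or with an infant up to 6 months; T1 at end of intervention, T2 and T3 at 6 and 12 months.

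**Assumptions, not in the document:** birth at 40 weeks' gestation; added sessions weekly, either after the core (in sequence) or during it (alongside); 6 months = 26 weeks and 12 months = 52 weeks. Weeks are counted from the first session.

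**Reproducing the ten weeks.** Ten weekly core sessions take 10 weeks, so the stated duration reproduces for the core. The whole programme is 10 + 3 + 3 = 16 sessions. For a postnatal woman it takes 10 weeks if the six added sessions run alongside the core, and 16 weeks if all are weekly and in sequence.

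**Antenatal women.** For a start at g weeks' gestation:

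- birth falls at programme week 40 − g;
- infant age at week 10 is 10 − (40 − g), negative before birth;
- the earliest programme end is max(13, 40 − g) + 3 in sequence, or max(10, 40 − g + 3) alongside.

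| Start, weeks' gestation | Birth, programme week | Infant age at week 10 (weeks) | Earliest end, in sequence | Earliest end, alongside |
|---|---|---|---|---|
| 12 | 28 | −18 | 31 | 31 |
| 20 | 20 | −10 | 23 | 23 |
| 28 | 12 | −2 | 16 | 15 |
| 30 | 10 | 0 | 16 | 13 |
| 36 | 4 | 6 | 16 | 10 |

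The baby is born within the ten weeks only if 40 − g ≤ 10, that is g ≥ 30. Below that, no spacing of sessions fits the mother–child module into ten weeks. The partner session that looks back to the birth is not imposed here; imposing it could only push the end later.

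**First reading: T1 after core session 10.** T1 is at week 10 for everyone, so T1–T3 are aligned from the start of treatment. For starts at 12, 20 and 28 weeks' gestation, T1 falls 18, 10 and 2 weeks before birth. The mother–child module then comes after the end-of-intervention assessment, and the QUIT cannot be completed at T1. T3 is at −18 + 52 = 34, −10 + 52 = 42 and −2 + 52 = 50 weeks postpartum. For women starting with an infant aged 0 to 26 weeks, T1 is at 10 to 36 and T3 at 62 to 88 weeks postpartum. A start at 36 weeks' gestation puts T1 at 6 weeks postpartum, so even among antenatal women some baseline-to-T1 changes span birth and some do not.

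**Second reading: T1 after the last mother–child session.** T1 is at about week 10–16 for postnatal women, and as late as week 23 or 31 for starts at 20 or 12 weeks' gestation. T2 and T3 shift by the same amount. Every antenatal woman's change to T1 spans birth, and no change in a woman enrolled and treated postnatally does.

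On both readings, one pooled ANOVA and one pooled Cohen's d at T1 combine the two kinds of change.

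**The case against.** The strongest reply is that the ten weeks is simply the core programme. Table 2 numbers it as sessions 1 to 10, ending in relapse prevention and consolidation, and lists the father and baby sessions separately as additional. Individual treatment also has ten sessions. Figure 1, a timeline, is not visible and may settle the matter. This has force: the core reading is coherent, and under it T1–T3 are aligned from the first session. It does not dispose of the point. Phase 4 lists the added sessions as part of what the intervention consists of and calls the mother–child sessions the last module. No figure can place sessions with the baby present before the birth.

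Three stronger inferences are tempting, and the documents do not support them.

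- A reader might infer that the intervention really takes 16 weeks. Only the core sessions are called weekly, and nothing says that the others follow in sequence.
- A reader might infer that T1–T3 necessarily fall at different elapsed times for antenatal and postnatal women. That holds only on the second reading.
- A reader might infer that the scheduling ambiguity is what confounds treatment with childbirth. The confounding comes from following a mixed antenatal and postnatal cohort without controls, and the article already lists the missing control group as a limitation. Any antenatal woman followed for 12 months crosses birth at some point. Anchoring time on the first session would therefore not remove it.

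It may also be said that subgroup modelling belongs in an analysis plan that is not shown. If that plan already separates antenatal from postnatal enrolment, that part is met. The undefined T1 and the mismatch with ten weeks remain.

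**Conclusion.** The concern holds in a limited form. The stated duration and the described content disagree for women starting before about 30 weeks' gestation, assuming birth at 40 weeks. For postnatal women they can be reconciled. The visible text leaves T1 open between two events, and each has a cost: intervention content and an unobtainable QUIT after or at T1 on one reading, or T1–T3 shifted later for antenatal women on the other. The week-23 and week-31 figures illustrate assumed schedules and are not established facts about the trial.

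On either reading, the effectiveness analysis as written does not isolate the antepartum effect that Hypothesis 4 is about. The size of any bias cannot be calculated: the article gives neither the antenatal share of treated women nor their gestation at start. Whether women in individual treatment receive the added modules is also unclear. The point is worth correcting before the effectiveness analysis, and it does not undermine the study as a whole.

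**What to change.** 1. Reconcile Procedures, Phase 4, the additional modules in Table 2, Phase 5 and the Data Analysis Plan on which event defines T1, and say whether it is the same in individual treatment. This should describe the care given, not change it. Which schedule is right is for the sponsor to state.
2. Use that one event for every woman, and record the date of each assessment and of delivery.
3. Report the pre–post effects separately for women enrolled antenatally and postnatally, or include enrolment status by time in the model. In either case, use pregnant or delivered status at each assessment and actual elapsed time, not only the nominal visit.
4. State at which assessments the QUIT applies for women who have not yet delivered.
5. Say plainly that, without a control group, change in antenatal women cannot be fully separated from the transition from pregnancy to postpartum, even with these steps.

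The cost is a clarification of the text, dates that should be easy to capture, a slightly more complex model, and less precise estimates within each group. Planned enrolment to treatment is 65, with 45 expected after loss to follow-up, so the subgroup estimates will be imprecise and should be presented with confidence intervals.

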**FIGURE 1 F1:**
[figure not shown]
Timeline.

#### Phase 1: Promoting Perinatal Mental Health Awareness

All mothers assisted in the healthcare centers are informed about the perinatal mental health problems that can occur during pregnancy and postpartum, and their impact on both the mother’s health and the baby’s development. Subsequently, mothers are invited to participate in the perinatal depression screening.

#### Phase 2: Screening for Psychosocial Risks, Depression, and Anxiety

Screening is performed once during the pre- or post-partum period, depending on the characteristics of each healthcare center. All mothers complete the Psychosocial and Clinical Assessment Form (Mirabella et al., 2016), the Italian versions of both the Edinburgh Postnatal Depression Scale (EPDS) (Cox et al., 1987; Benvenuti et al., 1999) and the Patient Health Questionnaire-9 (PHQ-9) (Kroenke et al., 2001) to evaluate depressive symptoms and the Italian version of the State-Trait Anxiety Inventory (STAI) (Spielberger et al., 1983; Pedrabissi and Santinello, 1992) to evaluate anxiety.

Mothers are required to complete the psychodiagnostic evaluation within one week of the date of positive screening results.

#### Phase 3: Psychodiagnostic Evaluation

All mothers undergo an interview with a clinical psychologist. Within the following week, in the case of clinician-generated diagnosis of perinatal depression and/or anxiety (according to the DSM-5 criteria), these mothers are further assessed using the Mini-International Neuropsychiatric Interview (MINI) Plus (Lecrubier et al., 1997; Sheehan et al., 1998) to confirm the diagnosis, the World Health Organization Quality of Life (WHOQOL) BREF (The Whoqol Group, 1998) to assess the quality of life and the Italian Questionnaires of Temperament (QUITs) (Axia, 2002) to assess the babies’ traits in temperament.

All mothers receive verbal feedback about the results of the psychodiagnostic evaluation. Depressed and/or anxious mothers are invited to participate in the intervention phase of the study. Whereas mothers with postpartum psychotic disorders, non-suicidal self-harm tendencies or suicidal ideation are sent to a psychiatric service and excluded from the study.

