### Hypotheses

(1)On the basis of the current literature (Underwood et al., 2016; Okagbue et al., 2017; Hahn-Holbrook et al., 2018), we expect to find a prevalence of perinatal depression within the range of 13–18%, with higher rates during pregnancy than in the first year following childbirth.(2)Based on previous research (Ghaedrahmati et al., 2017; Leach et al., 2017), we assume that the factors associated with a higher risk of perinatal depression and anxiety will include previous history of depression and anxiety, a negative attitude toward a recent previous pregnancy, high-risk pregnancy, young maternal age, limited social support, and financial problems.(3)In accordance with previous studies on screening for antenatal or postnatal depression (Yawn et al., 2009; Zhong et al., 2014; Santos et al., 2016), we expect that both the Edinburgh Postnatal Depression Scale and the Patient Health Questionnaire-9 will be reliable and valid scales for the assessment of perinatal depression.(4)Based on a prior Italian study (Mirabella et al., 2016) showing the effectiveness of Jeannette Milgrom’s (Milgrom et al., 1999) psychological intervention among women suffering from postpartum depression, we assume that intervention can be effective also with antepartum depressed women.(5)Given that the literature (Erickson et al., 2017) has offered ambiguous results on the association between prenatal maternal mental health and the development of infant temperament, we have no specific assumptions to this regard.

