### Measures

#### Edinburgh Postnatal Depression Scale

The EPDS (Cox et al., 1987) is the most widely used screening tool for depressive symptoms during the perinatal period (de Moraes et al., 2017; Ukatu et al., 2018). It is a self-rating scale containing 10 items about symptoms of depression such as anhedonia, feelings of guilt, lethargy, sleep disturbance and suicidal ideation. The answer to each item is on a four-point Likert scale with which mothers indicate the frequency with which they have experienced the corresponding symptom during the past 7 days. The total score ranges from 0 to 30, with higher scores indicating more severe depressive symptoms. The internal consistency of the Italian version of the EPDS (Cronbach standardized alpha) was 0.80 (Benvenuti et al., 1999), which is similar to the value reported by Cox in the first validation study (0.87). The sensitivity, specificity, and positive predictive value of the Italian version were recorded as 55.6, 98.9, and 90.9%, respectively, based on a cut-off score ≥12, making it a reliable and valid screening tool for perinatal depression. Furthermore, a recent study (Smith-Nielsen et al., 2018) found that a score of 11 or more is the optimal cut-off for depression according to both DSM-5 (American Psychiatric Association, 2013) and ICD-10 criteria (World Health Organization, 1992).

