### Sample Size

Assuming 10–15% prevalence of perinatal depression as measured by EPDS (Gavin et al., 2005; Melville et al., 2010) the minimum number needed of mothers to be screened is 500.

With regard to the clinical trial on the psychological interventions for perinatal depression and anxiety, the power calculation was based on detecting an effect size of medium magnitude (*d* = 0.55) at the follow-ups on the EPDS among the patients (Cohen, 1988). We calculated that a sample size of 45 patients would result in a power of 0.95 with alpha set at 0.05. To protect against an anticipated loss to follow-up of about 30% (Mirabella et al., 2016), we planned to enroll 65 patients.

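### Excluding women with self-harm or suicidal ideation from the whole study after screening would lower the prevalence estimate, and no case definition for prevalence is fixed

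*Protocol article*

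**What the plan says.** **Who leaves the study.** The Exclusion Criteria sit under the selection criteria for the whole cohort. They exclude mothers with psychotic symptoms, mothers with drug or substance abuse, and mothers if "they exhibit non-suicidal self-harming or suicidal behavior". The Phase 3 section invites depressed or anxious mothers to the intervention phase. It then says that mothers with postpartum psychotic disorders, "non-suicidal self-harm tendencies or suicidal ideation are sent to a psychiatric service and excluded from the study". By then these women have completed the EPDS, PHQ-9, STAI and psychosocial form in Phase 2.

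**How prevalence is measured.** Hypothesis 1 reads: "we expect to find a prevalence of perinatal depression within the range of 13–18" per cent. The Sample Size section begins "Assuming 10–15% prevalence of perinatal depression as measured by EPDS" and concludes that "the minimum number needed of mothers to be screened is 500". The Data Analysis Plan says prevalence will be calculated and compared, but names no instrument, cut-off or denominator. For the Italian EPDS, sensitivity, specificity and positive predictive value "were recorded as 55.6, 98.9, and 90.9%, respectively, based on a cut-off score ≥12". The same section adds that a recent study "found that a score of 11 or more is the optimal cut-off for depression".

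**Who is interviewed.** Phase 3 states: "All mothers undergo an interview with a clinical psychologist". Strengths and Limitations repeats that every mother had both questionnaires and an interview. Phase 2, however, times the psychodiagnostic evaluation from a positive screen.

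**The concern.** Excluding women at clinical risk from a treatment programme is a different matter from removing them from a prevalence count. Here the criteria are written at study level, and some of the women they cover are identified only after they have contributed screening data. The removal is related to the outcome: the Measures section notes that both the EPDS and the PHQ-9 contain a suicidal-ideation item. A cohort that loses such women will tend to show too little depression, yet Strengths and Limitations describes the sample as representative of pregnant women in Italy.

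The second issue is the missing case definition. The one place that connects prevalence to an instrument uses the EPDS, and the quoted sensitivity means that 44.4% of cases are missed at 12 or more (100 − 55.6). Hypothesis 1 could then appear to fail although it is true. The interview would avoid this if every woman has one, but the text disagrees with itself on that.

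**Working it through.** **The plan's own figure.** No precision target accompanies the 500, so it cannot be strictly reproduced. The 95% half-width 1.96·√[p(1−p)/500] is 2.6 points at p = 10% and 3.1 points at p = 15%. The figure also matches a case yield of 65/0.13 = 500, where 65 is the planned enrolment for the intervention. Either way, it governs precision or yield, not bias.

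**Effect of the exclusion.** Let p be the true prevalence, f the share of cases removed and g the share of non-cases removed. The remaining prevalence is p(1−f) / [p(1−f) + (1−p)(1−g)]. This is below p whenever f > g, that is, whenever cases are more likely to be removed than non-cases. With g = 0 it becomes p(1−f)/(1−pf). The documents give no value for f; 10–20% is an assumption.

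| True p | f = 10% | f = 20% |
|---|---|---|
| 13% | 0.117/0.987 = 11.9% | 0.104/0.974 = 10.7% |
| 15% | 0.135/0.985 = 13.7% | 0.120/0.970 = 12.4% |
| 18% | 0.162/0.982 = 16.5% | 0.144/0.964 = 14.9% |

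In 500 women with 75 cases (15%), these are 67.5/492.5 and 60/485. Over a wider assumed range of f = 5–30%, a true 15% reads as 14.4–11.0%. If the women's data are kept, the Phase 3 exclusion causes no bias.

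**Effect of using raw EPDS positives at 12 or more.** Inputs from the EPDS section are Se = 0.556 and Sp = 0.989. The apparent rate is Se·p + (1−Sp)(1−p).

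- p = 13%: 0.0723 + 0.0096 = 8.2%
- p = 15%: 0.0834 + 0.0094 = 9.3%
- p = 18%: 0.1001 + 0.0090 = 10.9%

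All three lie below the hypothesised 13–18%. The quoted inputs agree with one another: a predictive value of 90.9% implies a validation-sample prevalence of 16.5%.

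**How far this depends on the cut-off.** With an assumed operating point of Se 80% and Sp 90%, a true 15% reads as 0.120 + 0.085 = 20.5%. The direction therefore reverses.

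**Effect of interviewing only screen-positives.** If an EPDS of 12 or more were the only gate (an assumption), interview-diagnosed prevalence could not exceed 0.556 × 13% = 7.2% to 0.556 × 18% = 10.0%. Women positive on the PHQ-9 or STAI could recover some of the missed cases.

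**The case against.** The strongest reply is that nothing says the referred women's screening data are deleted. The Phase 3 sentence follows the invitation to treatment and can be read as directing these women away from the intervention. How excluded participants' data are handled may also be settled in a fuller document. This has some force, but the text separates the intervention phase from the study in adjacent sentences, and the Exclusion Criteria are study-wide too. Followed literally, these women leave the cohort.

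A reader might go further and infer that prevalence is biased low by construction because the study was sized on the EPDS. The documents do not support that. The 10–15% in Sample Size is already on the EPDS scale, and sizing affects only precision. No cut-off is fixed, Hypothesis 1 does not say how its 13–18% was measured, and an interview diagnosis made in all mothers would not inherit the EPDS sensitivity.

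Nor does a downward bias extend to anxiety. The quoted STAI figures (80.95%, 79.75%, predictive value 51.50%) imply a prevalence of about 21%, at which 0.8095 × 0.21 + 0.2025 × 0.79 = 33% screen positive.

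A reader might also infer that the exclusion lowers the estimated sensitivity of the EPDS and PHQ-9. That direction is not established. A fall requires the removed cases to be screen-positive more often than the cases that remain. Moreover, Phase 3 gives the MINI, the reference standard, only to women with a clinician's diagnosis. If only screen-positives are verified, sensitivity would be biased upward.

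**Conclusion.** The concern holds in a conditional form and is worth correcting, with medium confidence. As written, the exclusion removes women from the prevalence cohort on a feature tied to the outcome, and it biases depression prevalence down provided cases are removed more often than non-cases. At a true 15% and an assumed 10–20% of cases lost, the shortfall is 1.3–2.6 points. That is smaller than the 3.1-point half-width from 500 women, but it is systematic and would not shrink with a larger sample.

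The EPDS result (a true 13–18% reading as 8.2–10.9%) would be larger. It applies only if the estimate is the uncorrected rate at 12 or more and the 13–18% is a true diagnostic prevalence. Neither is stated. What is established is that the case definition and denominator are open, that the two exclusion wordings differ, and that the text conflicts on who is interviewed.

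**What to change.** 1. State that the psychosis, self-harm and suicidality exclusions apply to entry into the intervention phase only, with referral practice unchanged. Reconcile the Exclusion Criteria (behavior) with Phase 3 (ideation); which wording should stand is for the investigators.
2. Keep the screening and interview data already collected from referred women in the prevalence and risk-factor datasets, and report how many were referred. If any exclusion remains at enrolment, describe the population accordingly and soften the claim of representativeness.
3. Define depression prevalence as the clinician's DSM-5 diagnosis among all women screened. Report EPDS, PHQ-9 and STAI rates separately, labelled screen-positive, each with its cut-off. A misclassification-corrected (Rogan-Gladen) estimate is optional.
4. Reconcile Phase 2 (evaluation after a positive screen) with Phase 3 and Strengths and Limitations (all mothers interviewed).

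The cost is wording, plus a check that the consent form covers use of data from women who are later referred. If all mothers are interviewed as Phase 3 states, no new assessment is needed. If only screen-positives are interviewed, item 3 cannot be met from the planned data, and the plan must say so.
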